**Modulators**														
	Psychopathology (suspected diagnosis; SCID-5^g^ interview)					✓								
	State anxiety (STADI^h^ subscale)									✓				
	Prior knowledge about psychotherapy (FPTM^i^ subscale)					✓								
	Prior psychotherapeutic experience (G-EEE^j^ subscale)					✓								
	Satisfaction with therapeutic relationship (HAQ^k^ subscale)					✓								
	Time spent with the information brochure (single item)					✓				✓				
	Sociodemographic characteristics (single item)					✓								
	Intake of mental health medication (SCID-5 interview)					✓								

^a^TEX-Q: Treatment Expectation Questionnaire.

^b^MacCAT-T interview: MacArthur Competence Assessment Tool for Treatment.

^c^DCS: Decisional Conflict Scale.

^d^ACMTQ: Autonomous Motivation for Therapy Scale.

^e^CSQ-8: 8-item Client Satisfaction Questionnaire.

^f^At follow-up (T2 and T3), (serious) adverse events will be assessed by self-report instead of an interview.

^g^SCID-5: Structured Clinical Interview for Diagnostic and Statistical Manual of Mental Disorders-fifth edition.

^h^STADI: State Trait Anxiety Inventory.

^i^FPTM: Questionnaire on Psychotherapy Motivation.

^j^G-EEE: Generic Rating for Treatment Pre-Experiences, Treatment Expectations, and Treatment Effects.

^k^HAQ: Helping Alliance Questionnaire.

### Study Intervention

OIC will be conducted online by trained study psychologists (Master of Science) at T1. For the purpose of conformity with a realistic preliminary psychotherapeutic consultation, OIC will last no longer than 35 minutes. OIC includes theory-overarching information about psychotherapy, clarifying what psychotherapy is, which forms and settings of psychotherapy exist, and how to get access to psychotherapy. The clinician will provide information about psychotherapeutic techniques, possible therapeutic objectives, the efficacy, and underlying mechanisms of psychotherapy. All 4 psychotherapeutic approaches that are recognized by the German social law (cognitive-behavioral psychotherapy, brief psychodynamic psychotherapy, psychoanalytic therapy, and systemic psychotherapy) are considered in OIC concerning their key mechanisms and techniques. In line with recent recommendations [23,27], OIC will contain information about the possible negative effects of psychotherapy (eg, the temporary increase of psychological strain) and respective individual coping strategies. Prior experience with psychotherapy and treatment expectations will be addressed since both are suggested to induce placebo and nocebo effects, which, in turn, might influence psychotherapy outcomes [7]. The clinician will target participants’ expectations about outcome (ie, treatment benefit, positive and negative effects), process (ie, expected satisfaction, side effects, own impact, behavioral control), and their coping with potential side effects. In accordance with ethical demands [7,23], OIC will provide a realistic and nondeceptive yet positive description of psychotherapy.

During OIC, the strategies of framing, contextualization, and shared decision-making will be applied. Framing strategies as described by Barnes et al [20] will be applied by embedding information about the possible negative effects in information about the overall effectiveness of psychotherapy [7,28]. Information will be formulated gain-framed. Contextualization will be used to adapt evidence-based information about psychotherapy to the individual information needs as well as the psychological and living conditions of the participant [6]. In line with the shared decision-making approach, participants will be informed about treatment alternatives (eg, psychopharmacotherapy) and will be invited to express their views and preferences [29]. Participants will be actively involved in the discussion of options. A balanced relationship between the clinician and the participant will be supported by an empathic attitude of the clinician. As a multimodal presentation might increase the comprehension of information and is assumed to elicit larger framing effects on the reduction of nocebo side effects [20], information will be given orally with additional support of visual information cards.

### TAU as a Comparator

To investigate the clinical significance of the newly developed OIC, a TAU condition will be used as a comparator. In both trial conditions, participants will receive an information brochure about psychotherapy from the Federal Chamber of Psychotherapists in Germany as TAU [30]. Participants may decide on their own whether and if so, how long they want to engage with the 80-page information brochure for psychotherapy patients.

### Randomization

Stratified permuted block randomization with a block size of 4 permutations will be used to randomize participants 1:1 to the OIC and TAU conditions. Stratification will be based on prior experience with psychotherapy (no vs positive vs negative prior experience) to ensure that individuals with heterogeneous treatment experiences are balanced in both arms. Before the first enrollment, the randomization sequences will be generated by a researcher who is not involved in the study conduction by using a web-based program. At the end of the first web-based study visit, the responsible study psychologist initially determines the type of prior experience with psychotherapy by evaluating the information given by each participant. The randomizing officer will then conduct the allocation of each pseudonymized study case according to the randomization plan. Finally, the randomizing officer will inform the respective study psychologist about the group membership on a case-by-case basis.

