#### Inclusion and Exclusion Criteria

Participants need to (1) be older than 18 years of age, (2) have an indication for psychotherapy, (3) have an email account and a web-connected device with a camera and a microphone, and (4) provide informed consent for study participation and the use of an audio record. The indication for psychotherapy will be operationalized by at least one suspected diagnosis according to the Diagnostic and Statistical Manual of Mental Disorders-fifth edition (DSM-5) [25].

Exclusion criteria are (1) a current outpatient or inpatient psychotherapy, (2) utilization of probatory sessions for psychotherapy within the last 4 weeks, (3) insufficient language comprehension, (4) insufficient attention performance or cognitive capacity to participate in the interviews and OIC, and (5) acute suicidality. Exclusion criteria (3) and (4) will be evaluated by the study psychologist during the telephone screening and the clinical interview. Based on a criteria-led graduated scheme, acute suicidality will be evaluated by the study psychologist within the clinical interview. In case of acute crises, further predefined steps for action will be initiated.

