### Blinding

Due to the nature of the study, neither participants nor the responsible study psychologists can be fully blinded toward the group membership. The assessment and analysis of the capacity to consent and the adverse events, however, will be carried out by researchers who are blinded regarding the randomization and do not otherwise interact with the respective participants throughout the entire course of the study. Questionnaire-based outcomes will be assessed pseudonymously via a web-based software, and the researcher conducting the statistical analyses will be blinded toward the randomized group allocation.

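### A fixed block size of 4 lets staff who know it and the earlier allocations in a stratum deduce up to one third of assignments in advance, and the psychologist who sets the stratum is told allocations

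*Protocol article*

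**What the plan says.** The Randomization section of the protocol article specifies "Stratified permuted block randomization with a block size of 4 permutations", with a 1:1 ratio. The lists are stratified by prior experience of psychotherapy in three categories (none, positive, negative).

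The same section sets the order of events. At the end of the first visit, "the responsible study psychologist initially determines the type of prior experience with psychotherapy by evaluating the information given by each participant". A randomizing officer then allocates the pseudonymized case from the plan. Finally, "the randomizing officer will inform the respective study psychologist about the group membership on a case-by-case basis". The sequences are produced before the first enrolment by a researcher who takes no part in running the study.

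Other sections describe the psychologist's position:

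- **Inclusion and Exclusion Criteria:** insufficient language comprehension and insufficient attention or cognitive capacity "will be evaluated by the study psychologist during the telephone screening and the clinical interview". Acute suicidality is also assessed by the study psychologist, using a criteria-led scheme.
- **Blinding:** "neither participants nor the responsible study psychologists can be fully blinded". Blinded assessors cover capacity to consent and adverse events.
- **Primary Outcome Measure:** treatment expectation is a self-rating.
- **Study Intervention and Bias Control:** study psychologists are mentioned in the plural, without a number.
- **Results:** enrolment began in August 2021 and data collection was expected to end in December 2022, so the block size was put in print while the trial was described as still running.

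**The concern.** Allocation concealment needs more than a list that nobody can see. Whoever decides on eligibility and stratum must also be unable to work out the next assignment. With one short block length throughout, the end of each block follows from its beginning. Here the same role decides on some exclusions, chooses which of three lists the participant enters, and learns the results of earlier draws.

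If the next assignment can be foreseen, judgements on borderline eligibility, or on whether mixed experience counts as positive or negative, can drift with the expected arm, even without intent. The primary outcome is self-rated by participants who are not fully blinded, so concealment is one of the few protections left. The Study Intervention section also says that prior experience may induce placebo and nocebo effects, so steering on that variable would not be neutral.

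**Working it through.** The article gives no predictability figure to reproduce, so the size is derived here.

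**Inputs from the article:** block size 4, ratio 1:1, three strata, 122 participants. The article's phrase attaches the number 4 to permutations, but a 1:1 block of length 4 has 4!/(2!·2!) = 6 permutations. It is read here as block length 4.

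**Assumption, not in the article:** the number of psychologists k, taken from 1 to 6.

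**1. Deducible assignments, observer fully informed.** An assignment is certain once one arm has used its two places in the block.
- 2 of the 6 permutations (two of one arm, then two of the other) fix the last two places.
- The other 4 fix only the last place.
- Expected number certain per block: (2×2 + 4×1)/6 = 1.33 of 4, or 33.3%.

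A simulation of 122 participants in three strata, allowing for incomplete last blocks, gives 32% to 33%, or about 40 participants.

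**2. Correct guesses, same observer.** The best guess is right with probability 1/2, 2/3, 2/3 and 1 at places 1 to 4. The sum is 17/6; divided by 4 this is 17/24 = 70.8%.

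**3. Deducible assignments when each psychologist knows only their own cases.** Suppose cases fall at random among k psychologists and block boundaries are known. The psychologist handling the next case must also have handled both cases that exhausted the arm, which has probability 1/k². The share is therefore (1/3)/k²:

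| k | Share certain | Of 122 |
|---|---|---|
| 1 (or pooled knowledge) | 33.3% | about 40 |
| 2 | 8.3% | about 10 |
| 3 | 3.7% | about 5 |
| 4 | 2.1% | about 3 |
| 6 | 0.9% | about 1 |

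Simulation agrees (8%, 4%, 2% and 1% for k = 2, 3, 4 and 6). Without knowledge of the block boundaries the shares would be lower still.

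**4. A participant who could fit either of two strata.** For a fully informed observer, the next draw in one list is certain to be a given arm with probability 1/6 (half of 1/3). Treating the lists as independent, at least one of two is certain to give that arm with probability 1 − (5/6)² = 31%. How often a participant fits two strata is unknown.

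**5. Effect of varying the block size.** The observer is assumed to know every earlier allocation in the sequence and the set of possible sizes, but not which size each block has.

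| Design | Certain | Best guess correct |
|---|---|---|
| Fixed 4 | 33% | 71% |
| Random 4 and 6 | about 5% | about 69% |
| Random 4, 6 and 8 | about 2% | about 67% |

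**The case against.** The strongest reply is that the fully informed observer may not exist. The officer informs only the respective psychologist, case by case, and there are several psychologists. Nothing in the article says that they pool allocations or were told the block size. This stands, and it makes one third an upper bound. A reader might infer that a psychologist is told every allocation, or that a third of assignments were in fact known. The text supports neither.

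There are real safeguards: an uninvolved sequence generator, a separate officer handling pseudonymized cases, and eligibility, baseline assessment and stratum all settled before allocation. The indication is verified by structured interview, and suicidality is judged by a criteria-led scheme. These narrow the room for discretion and stop anyone reading the list ahead. They do not stop deduction from assignments already disclosed, and fixing the stratum first does not help if the person fixing it can foresee the draw.

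The Statistical Analyses section has baseline expectation in the primary model, lists type of prior experience as a candidate covariate, and uses intention to treat; the analyst is blinded. Selection on baseline expectation would be visible and partly adjusted for. Selection on unmeasured differences would not.

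A classification rule for prior experience may exist in the full protocol, and the prior-experience subscale in Table 1 may be the information the psychologist evaluates. This is fair, and makes the stratum rule a secondary point.

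Lastly, varying block sizes barely lowers the success of guessing, and few blocks may be left. The third follow-up falls about three and a half months after the first visit, so enrolment would close around mid-September 2022 if data collection ends in December. Both points stand and limit what the change can achieve.

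**Conclusion.** The point holds as a vulnerability in the design. One fixed block size of 4, combined with a study psychologist who is not fully blinded, judges exclusions, determines the stratum and then learns the allocation, leaves assignments partly predictable. The size depends on facts the article does not give: up to 33% deducible if staff know the block size and all earlier allocations in the stratum, and roughly 8% to 1% if 2 to 6 psychologists each know only their own cases. The 31% figure for a participant who fits two strata also needs full knowledge of both lists.

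A reader might go on to infer that selection bias has occurred. The article gives no evidence of that, and the point does not depend on it. The change is a cheap improvement that should be made while blocks remain unused.

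**What to change.** - **Block sizes:** have the independent researcher regenerate the unused blocks in the three lists with sizes drawn at random, for example 4, 6 and 8, and do not disclose the sizes to study staff.
- **Stratum:** assign it by a fixed rule from the prior-experience data already collected at T0, and log it before the officer is contacted. If the full protocol already contains such a rule, cite it.
- **Participants already randomized:** report the fixed block size as a limitation, with the number of study psychologists and whether they knew the block size or each other's allocations.

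The cost is part of three lists and a line or two of text. The downside is a slightly larger possible arm imbalance at the end of each stratum: an incomplete block of 8 can leave the arms up to 4 apart, against 2 for a block of 4.

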### Statistical Analyses

Linear mixed modeling for repeated measures will be conducted for the hypothesis referring to the primary outcome. Following the intention-to-treat approach, all randomized participants will be included in the analysis to avoid attrition bias. The model will contain one between-subject factor treatment (OIC + TAU vs TAU) and one within-subject factor time (T0, T1, and T2). Before linear mixed modeling, additional variables (eg, respective baseline scores, type of prior experiences with psychotherapy, prior knowledge about psychotherapy, satisfaction with the therapeutic relationship, state anxiety, the time of occupation with the information brochure) will be checked for significant associations with the respective outcomes to identify potential covariates. If there are additional covariates, they will be included in the linear mixed model. Group differences will be checked using Tukey posthoc tests. In case of imbalanced group sizes, Bonferroni-corrected posthoc tests will be carried out instead.

The analytical strategy of fitting linear mixed models will also be applied to all analyses, including secondary outcomes. Three exceptions for the described analytical strategy will be analyses including the secondary outcomes of capacity to consent, satisfaction with received information, and (serious) adverse events, for which group differences at postassessment will be examined by an independent sample two-sided *t* test, a Welch *t* test, or a Mann-Whitney *U* test. Intergroup differences at baseline will be detected using independent sample two-sided *t* tests, Welch *t* tests, or Mann-Whitney *U* tests (for continuous variables) and Pearson chi-square tests (for categorical variables). Partial eta squared will be reported for estimating the proportion of explained variance, with *η^2^*=0.01 indicating small, *η^2^*=0.06 indicating moderate, and *η^2^*=0.14 indicating large effects [40]. Cohen *d* will be determined as a measure of effect size for pairwise comparisons (standardized mean differences) by dividing the mean score difference between the groups to be compared by the pooled standard deviation. According to Cohen [40], values of *d*=0.2, *d*=0.5, and *d*=0.8 are considered to indicate small, medium, and large effect sizes, respectively.

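### The randomization stratum is left out of the two-group tests and enters the mixed models only if a significance check selects it, so some secondary tests are mildly conservative

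*Protocol article*

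**What the plan says.** The Randomization section describes the allocation method: "Stratified permuted block randomization with a block size of 4 permutations will be used to randomize participants 1:1". It names a single stratification factor with three levels: "Stratification will be based on prior experience with psychotherapy (no vs positive vs negative prior experience".

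The Statistical Analyses section then fixes only two terms in the mixed model: "The model will contain one between-subject factor treatment (OIC + TAU vs TAU) and one within-subject factor time (T0, T1, and T2". The stratification factor appears further on, in a list of candidates: "additional variables (eg, respective baseline scores, type of prior experiences with psychotherapy, prior knowledge about psychotherapy". These candidates "will be checked for significant associations with the respective outcomes to identify potential covariates", and entry depends on the result: "If there are additional covariates, they will be included in the linear mixed model".

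Three sets of secondary outcomes are handled outside the model: "capacity to consent, satisfaction with received information, and (serious) adverse events, for which group differences at postassessment will be examined". The tests offered are the two-sample t, Welch t and Mann-Whitney U tests, none of which has a place for the stratum. Nothing in the article commits to keeping the stratum whatever the check shows.

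**The concern.** Stratified blocks make the arms nearly equal within each level of prior experience. Differences between levels therefore contribute almost nothing to the chance variation of the treatment difference. An analysis that omits the stratum still counts those differences as noise. Its standard error is then larger than the real sampling variation, its intervals are too wide, and it rejects a true null less often than 5% of the time. Precision gained by the design is lost in the analysis.

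The two-group outcomes are the most exposed. Table 1 schedules the MacCAT-T and the CSQ-8 at T1 only, so there is no baseline value to absorb stratum differences, and the covariate check feeds only the mixed models. For the modelled outcomes, checking each outcome separately means that the adjustment set can differ from one outcome to the next and is unknown until the data are seen.

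**Working it through.** **Inputs from the article.** Three strata, blocks of 4, 1:1 allocation (Randomization). Two-sided α = 0.05 (Statistical Analyses). 106 evaluable participants for 80% power at f = 0.125, and 122 randomized (Sample Size).

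**Inputs assumed.** R², the share of outcome variance explained by the stratum, is not given. It is varied from 0 to 0.30, with stratum shares of 40/40/20% in the simulations.

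**The plan's own figure.** For a repeated-measures interaction, λ = f²·N·m/(1−ρ), df1 = (k−1)(m−1), df2 = (N−k)(m−1). With k = 2 groups, m = 3 times and an assumed ρ = 0.5 with sphericity, N = 106 gives power 0.807, so 106 is reproduced. The calculation has no stratum term, and adding the stratum to the analysis does not change it.

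**Two-group tests, by formula.** Let the outcome variance be σ² and the within-stratum variance (1−R²)σ². With arms balanced in each stratum, the treatment difference has true variance of about 4(1−R²)σ²/N, while the unadjusted test uses about 4σ²/N. Hence:

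- SE ratio = 1/√(1−R²)
- true type I error = 2·[1 − Φ(1.96 × ratio)]

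At R² = 0.05 the ratio is 1/√0.95 = 1.026 and the error 2·[1 − Φ(2.011)] = 4.4%. At R² = 0.15 the ratio is 1/√0.85 = 1.085 and the error 2·[1 − Φ(2.126)] = 3.4%.

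**Single-time-point tests, by simulation.** Stratified blocks of 4, N = 106, 10,000 trials per null scenario:

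| R² | Formula: SE ratio / type I | Simulated SE ratio | Type I, t test | Type I, always adjusted | Type I, adjusted if significant | Stratum selected |
|---|---|---|---|---|---|---|
| 0 | 1.000 / 5.0% | 1.00 | 4.8% | 4.8% | 4.9% | 5% |
| 0.05 | 1.026 / 4.4% | 1.01 | 4.7% | 5.2% | 5.2% | 54% |
| 0.10 | 1.054 / 3.9% | 1.05 | 3.6% | 4.7% | 4.7% | 86% |
| 0.20 | 1.118 / 2.8% | 1.11 | 2.9% | 5.2% | 5.2% | 99.6% |
| 0.30 | 1.195 / 1.9% | 1.19 | 2.0% | 4.7% | 4.7% | 100% |

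Formula and simulation agree within simulation error. For an illustrative difference of 0.55 SD, power at R² = 0.05 / 0.10 / 0.20 / 0.30 is 80 / 82 / 83 / 84% without the stratum and 82 / 84 / 88 / 92% with it.

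The check-then-include columns are a stand-in for the modelled outcomes, since the plan does not apply the check to the two-group tests. At N = 122 (8,000 trials; R² = 0.05 / 0.10 / 0.15) the check selects the stratum in 60 / 91 / 99% of trials, and type I error is 5.3 / 4.9 / 5.0%, the same as when the stratum is always included.

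**Treatment-by-time test over T0, T1 and T2, by simulation.**

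- Stratum effect constant over time (R² = 0.10 and 0.30): type I error 5.6% and 4.7% without stratum by time, 5.5% and 4.7% with it. The constant effect cancels.
- Stratum explains 5 / 10 / 20% of the change over time: 4.4 / 3.8 / 2.5% without stratum by time, 5.1 / 5.0 / 4.9% with it.

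**The case against.** The strongest reply is that the plan does not discard the stratum. It names it as a candidate and promises to include whatever the check finds. A strongly prognostic stratum is nearly always found: in 99% of simulated trials at R² = 0.15 and N = 122. Where it matters most, the rule therefore behaves like always adjusting. This stands for the modelled outcomes. It does not reach the two-group tests, to which the check does not apply.

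A second reply is that the hypotheses in the Introduction concern change from T0 to T2, so the primary test is in effect treatment by time, and a stable difference between strata drops out. This also stands. What remains is the case in which prior experience predicts change in expectations. The article does not quantify that, and a stratum main effect alone would not absorb it.

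A third reply is that the loss is small and in the safe direction. At R² = 0.05 it is barely visible, and nothing in the article suggests that prior experience explains as much as 15% of the variance in capacity to consent or in satisfaction. That is fair, and it limits the weight of the point.

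A reader might also infer that the stratum was chosen because it is expected to predict the primary outcome. The Randomization section gives only balance of differing treatment experiences as its reason. The Study Intervention section links prior experience to placebo and nocebo effects, but as a reason to address it in the consultation.

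Lastly, one could say that an article may leave such detail to an analysis plan. Here, however, the article states the rule, and the rule makes a design factor optional.

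**Conclusion.** The point holds, with limited reach. In the two-group comparisons of capacity to consent, satisfaction and (serious) adverse events, omitting the stratum makes the tests conservative. For an assumed R² of 0.05 to 0.15, the standard error is about 3% to 8% too large and type I error is about 4.4% to 3.4% at a nominal 5%. If the stratum explains nothing, there is no effect. The formula describes mean comparisons; for rank tests and adverse-event ratings only the direction carries over.

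A reader might apply these figures to the primary analysis, or conclude that its error rate is wrong. The article does not support that. The figures assume a single time point and a stratum that is always left out, whereas the plan's rule stays near 5% in simulation and a time-constant stratum effect cancels from the treatment-by-time contrast. The primary test loses something only if the stratum predicts change. Nowhere does the omission raise the false-positive risk or bias the estimate. The remaining weakness in the mixed models is an adjustment set that depends on the data and may vary between outcomes.

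**What to change.** State that the stratum recorded at randomization (none, positive or negative prior experience) is a fixed factor in every treatment comparison, whatever its significance, and remove it from the list of candidates to be checked.

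- Mixed models: include stratum and stratum by time.
- MacCAT-T and CSQ-8: use linear regression on treatment and stratum in place of the t or Welch t test.
- Where a Mann-Whitney U test would have been used, including for adverse-event ratings: use a stratified rank test (van Elteren).

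The cost is wording in the analysis section and 3 − 1 = 2 degrees of freedom, plus (3 − 1)(3 − 1) = 4 for stratum by time over three assessments. Sample size, data collection and trial conduct are unchanged.
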